### Sample size

The sample size was calculated using Pearsons’s Chi-square test, yielding *N* = 81 participants per group to be able to show noninferiority between treatments, accepting a non-inferiority margin of 20% difference to the reduction demonstrated in the original LiFE study [29]. Considering a drop-out rate comparable to the original LiFE study of 25% for all assessments [29], actually *N* = 108 participants per group are needed. To account for an additional variance due to the multi-centre design we increased the sample size by 10% and added another safety margin, coming out with an envisaged sample of a total of *N* = 300 community-dwelling participants to take part in the study: *n* = 150 at both study sites, i.e., the Network Aging Research (Heidelberg, Germany) and the Robert Bosch Hospital (Stuttgart, Germany).

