### Recruitment

Participant recruitment started in April 2018; last participants will be recruited in June 2019. Participants will be recruited using data from the municipal registration offices in Heidelberg and Stuttgart. Recruitment will be performed via mail, with waves of 300 or 1000 letters being sent to randomly selected persons in the registry. In Heidelberg, residents from all city districts will be eligible to receive study information and a flyer with a prepaid response postcard to send back to the study centre if interested in participating in the study; in Stuttgart, due to the city’s much larger size compared to Heidelberg, residents from only one city district are contacted. To facilitate contacting the study centres, persons interested in the study may also use a contact form on the project website (http://www.life-alltagsuebungen.de) which was developed to enhance the project’s reach and public visibility. In addition, additional actions will be undertaken to support participant recruitment: In Heidelberg and Stuttgart, flyers and brochures will be distributed in pharmacies, physiotherapy and medical practices; press releases and articles will be launched in regional and district newspapers; lectures will be given at local public organisations concerned with health and aging. In Stuttgart, a cooperating health insurance company is going to contact their members in the desired age group living in the relevant city district via mail.

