### Statistical analyses

Statistical analyses will follow the ICH Harmonized Tripartite Guideline “Statistical Principles for Clinical Trials” E9 [64]. Based on the trial of Clemson et al., we expect a decrease in fall incidence (expressed as falls per amount of PA) of 79.4% for LiFE [29]. A one-sided Pearson’s chi-square test will be used to test noninferiority with α = 0.05 in the fall incidence between LiFE and gLiFE with a noninferiority margin of − 15.9%.

All main analyses will be done according to the intention-to-treat principle, which will include all randomized participants in the analysis dataset for whom a baseline assessment was conducted, regardless of their adherence to and compliance with the assigned treatment. Participants who withdrew or dropped out are requested to participate in follow-up assessments; those who are lost to follow-up will be included in the full analysis set by imputing their missing data. Secondary analyses will provide a more detailed insight on which dimensions both treatments are effective to deepen the understanding of trial results. Understanding the underlying physiological pathways in both formats will increase knowledge on the effectiveness of the intervention components and strategies and thereby improve the design and implementation of both LiFE treatments. Additionally, sensitivity analyses will be performed to explore the effect of missing values and attrition during treatment:Per-protocol analysis of the dataset restricted to all participants with available measurements for the primary variables and no protocol violations.If the number of missing values is substantial (higher than 5% for a given variable), a sensitivity analyses will be conducted for imputing missing values.

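### The sample is enlarged for centre variance, but the named primary test pools the two centres; stratifying the comparison by centre is a small improvement at almost no cost

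*Protocol article*

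**What the plan says.** Under Sample size, the protocol article reaches 81 participants per group, raises this to 108 for 25% drop-out, and continues: "To account for an additional variance due to the multi-centre design we increased the sample size by 10" per cent. A further safety margin of unstated size brings the total to 300, with 150 at each site.

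Under Statistical analyses, the primary comparison is named: a one-sided Pearson's "chi-square test will be used to test noninferiority with α = 0.05 in the fall incidence between LiFE and gLiFE", with a margin of −15.9%. No stratum, covariate or centre term accompanies it.

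Under Recruitment, the centres differ. In Heidelberg all city districts are eligible. In Stuttgart "residents from only one city district are contacted", and a health insurer also writes to its members there. Table 2 gives different gLiFE venues: the research institute in Heidelberg and rented rooms in Stuttgart. Allocation and blinding describes computer-generated blocks of variable size and does not mention centre.

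**The concern.** The plan expects centre to matter and recruits for it, then names a test that cannot use the one piece of centre information everybody has. What follows depends on how the blocks are arranged, which the article does not say.

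- **Blocks within centre.** The arms are balanced on centre, so a difference in level between centres does not affect the arm difference. The pooled variance still contains it, so the pooled interval is slightly too wide.
- **Blocks across centres.** Chance imbalance in centre between the arms moves the estimate that is compared with the margin.

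A centre-stratified analysis deals with both. At stake is some precision, and an estimate free of chance centre imbalance, in a noninferiority comparison where the position of one confidence limit decides the result.

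**Working it through.** **Inputs.** From the article: expected figure 0.794 ("we expect a decrease in fall incidence (expressed as falls per amount of PA) of 79.4% for LiFE"); margin 20% of that, 0.2 × 0.794 = 0.1588, stated as 15.9%; one-sided α = 0.05; drop-out 25%; 10% for the multi-centre design; 150 per arm and 150 per site. Assumed: 0.794 is a proportion and equal in both arms; power is 80% (not stated); the centres are of equal size; the centre difference D takes a range of values, since none is given.

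**The plan's own figure.** n = 2 × 0.794 × 0.206 × (1.645 + 0.842)² / 0.159² = 80.0003, rounded up to **81** per group. At 90% power the formula gives 111, so 80% is the likely basis. Then 81 / 0.75 = **108**, and 108 × 1.10 = 118.8 per group, or about 238 in total. The rest, up to 300, is the safety margin.

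**Variance due to centre.** Pooled variance V = 0.794 × 0.206 = 0.163564. For two equal centres, V = within-centre variance + (D/2)². The centre share is therefore (D/2)²/V. Power is Φ(0.159/√(2v/n) − 1.645), with v = V for the pooled test and v = V − (D/2)² for the stratified test. Pooled power is 0.804 at n = 81, and 0.904 at n = 112.5 (150 less 25%).

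| D (points) | Centre share of V | Stratified n per group (pooled 81) | Stratified power, n = 81 | Stratified power, n = 112.5 |
|---|---|---|---|---|
| 5 | 0.4% | 80 | 0.806 | 0.905 |
| 10 | 1.5% | 79 | 0.810 | 0.908 |
| 15 | 3.4% | 78 | 0.816 | 0.912 |
| 20 | 6.1% | 76 | 0.826 | 0.919 |
| 24 | 8.8% | 73 | 0.835 | 0.925 |

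**Simulation** (82 per group, 200,000 runs per case).

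- D = 10 points: power 0.817 pooled and 0.820 stratified with centre-balanced allocation; 0.815 and 0.817 without it.
- D = 20 points: 0.823 and 0.834 with balance; 0.815 and 0.833 without.
- Mean standard error at D = 20: 0.0627 pooled, about 0.0605 stratified.

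Part of this simulated gain is not real. The stratified estimate's actual SD is 0.0612, a little above its estimated standard error, because plug-in variances in four small cells are biased slightly downwards.

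Taking formula and simulation together, D = 10 is worth about 0.2 to 0.6 points of power and D = 20 about 1 to 2 points.

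**Chance imbalance if blocks cross centres.** SD of the shift = D × √(0.25 × 2/150) = D × 0.0577, which is 0.58 points at D = 10 and 1.15 points at D = 20, against a margin of 15.9 points.

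**The case against.** The strongest case against has four parts.

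1. **Condensed article.** Strata and covariates are often left to the analysis plan, which is not shown. This holds for the block lists and any display of results by centre, so neither is part of the point. It does not hold for the test: the article names a specific test, the sample size rests on the same one, and it cannot use centre.

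2. **Enlarging the sample and then testing pooled is coherent.** This stands. A reader might infer that the sample size and the analysis contradict each other. They do not: allowing for a variance that the test leaves in place is inefficient but consistent.

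3. **The 10% is an allowance, not a measurement.** This also stands. A reader might take 1 − 1/1.1 = 9.1% as the centre share of the variance and count 118.8 − 108, about 11 participants per arm, as recoverable. The article does not support that. It gives no centre difference and does not say which component of variance the 10% covers. V at the overall 79.4% already contains any level difference, and a full 10% excess would need centres about 24 points apart.

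4. **The effect is slight and the outcome form uncertain.** Pooled power is already 0.904 at 112.5 evaluable per arm. With balanced centres the pooled test errs on the cautious side. Different recruitment routes do not prove different outcomes, and the article describes 79.4% as a decrease in falls per amount of physical activity, so treating it as a proportion is a working assumption. All of this limits the size of the gain; none of it favours the pooled test.

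**Conclusion.** The point holds as a minor improvement. The article expects centre variance, centre is known for all participants, and the named primary test cannot use it. A centre-stratified comparison is at least as good for practical purposes: about 0.2 to 0.6 points of power for a 10-point centre difference, about 1 to 2 points for a 20-point difference, and removal of a chance shift with an SD of about 0.6 to 1.2 points if blocks are not within centre. These sizes rest on treating 79.4% as a proportion, on 80% power, on equal centres and on assumed centre differences.

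A centre term removes only differences in level between centres. It does not remove variation of the treatment effect between centres, or clustering within gLiFE groups; if the 10% was meant for those, stratification does not replace it. The trial is not underpowered on its own inputs because of this point, and no conclusion is shown to change.

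**What to change.** In Statistical analyses, state that the primary noninferiority comparison is stratified by centre. If a proportion is kept, use a Mantel-Haenszel type difference with its confidence limit set against the 15.9% margin. Otherwise, put a centre fixed effect in the primary model and report the arm effect on the scale on which the margin is defined.

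Leave the sample size as it is. One clause in Sample size saying which variance the 10% is meant to cover would help the reader.

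The cost is a sentence of analysis wording and one degree of freedom. No data, participants or procedures are added. The change does not depend on how the blocks were arranged, so it can be made while the trial is running, provided it is fixed before the outcome data are analysed.

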### Recruitment

Participant recruitment started in April 2018; last participants will be recruited in June 2019. Participants will be recruited using data from the municipal registration offices in Heidelberg and Stuttgart. Recruitment will be performed via mail, with waves of 300 or 1000 letters being sent to randomly selected persons in the registry. In Heidelberg, residents from all city districts will be eligible to receive study information and a flyer with a prepaid response postcard to send back to the study centre if interested in participating in the study; in Stuttgart, due to the city’s much larger size compared to Heidelberg, residents from only one city district are contacted. To facilitate contacting the study centres, persons interested in the study may also use a contact form on the project website (http://www.life-alltagsuebungen.de) which was developed to enhance the project’s reach and public visibility. In addition, additional actions will be undertaken to support participant recruitment: In Heidelberg and Stuttgart, flyers and brochures will be distributed in pharmacies, physiotherapy and medical practices; press releases and articles will be launched in regional and district newspapers; lectures will be given at local public organisations concerned with health and aging. In Stuttgart, a cooperating health insurance company is going to contact their members in the desired age group living in the relevant city district via mail.

### Allocation and blinding

After completion of baseline assessments, participants will be randomised in either gLiFE or LiFE by the study coordinators in computer-generated blocks of variable size. To facilitate the gLiFE organisation process, all participants will be asked during the inhouse screening at which weekdays they have time to participate in a morning session (9.30 AM to 11.30 AM) or afternoon session (2.00 PM to 4.00 PM). gLiFE groups will be started once at least 8 and up to 12 persons are randomly allocated to this arm of the intervention and have a match in their schedule. LiFE participants can start the intervention immediately after the 9-day PA recording period has ended. All research staff will be eligible to perform telephone screenings, inhouse screenings, and baseline assessments prior to randomisation. Follow-up assessments after randomization will be performed by assessors blinded towards group allocation. To ensure blinding of assessors, the database used in this study will only show information not related to the intervention when assessors are logged in. For trainers and study coordinating staff, all information will be unlocked. Outcome measures which identify group allocation such as evaluation of intervention sessions will be collected by unblinded research staff.

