#### Individual LiFE (LiFE)

In LiFE, the program will be taught in seven individual home visits within 11 weeks, as described in the original LiFE program manual [35]. Each home visit is going to take between 1 and 1.5 h. Trainers are going to present a total of five balance activities, seven strength activities for the lower extremities, and two activities to increase general PA are presented. Participants are going to learn how to implement the LiFE activities into their daily routine and how to independently execute the activities, including selection, upgrading, and identification of daily situations to integrate activities. In addition to the home visits, all participants are going to receive two ‘booster telephone calls’ four and 10 weeks after the last intervention session.

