#### Group LiFE (gLiFE)

gLiFE will consists of seven group sessions (*n* = 8–12 participants) which are held over the course of 11 weeks, with a duration of about 2 h per session. Each session is going to be led by one main and one co-trainer. In all group sessions, trainers are going to teach the participants how to perform and integrate LiFE activities into their personal daily routine in congruence with LiFE. After the group sessions have ended, participants will also receive two booster telephone calls as in LiFE (see Fig. 1).

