Although Clemson and colleagues adhered to the common practice of evaluating fall prevention trials based on fall rates per total observation time (e.g., falls per person year) [29], in this study, we will estimate falls per risk exposure time, i.e., per walking duration and energy expenditure. Considering that, as the LiFE program promotes PA then it also enhances risk exposure of participants, the relationship of PA and falls might be a more adequate outcome rather than the rate of falls per total observation time [26, 75]. This is more likely an appropriate analysis considering that both physical inactivity and high falls risk are negatively associated with healthy life expectancy [76].

As a limitation, it has to be acknowledged that in such a trial, it cannot immediately be distinguished between effective and ineffective treatment due to the lack of (placebo or “sham”) control, i.e., both treatments/interventions could be ineffective [77]. However, the LiFE study by Clemson et al. has shown its high value and effectiveness, even though in only one large trial.

Concluding, this study will be of high practical relevance as noninferiority of gLiFE would facilitate nationwide implementation due to lower financial and personnel requirements. This is of special importance in the face of the large number of older people in need of preventive measures which have to be provided by a small number of therapists, especially when it can be expected that the ratio of therapists to patients will increase. Due to the lack of knowledge on the participants’ personal (home) environment and the consequential limitation of individualization options of LiFE activities in the group (gLiFE), we do not expect the group format to be superior to LiFE. However, LiFE activities are graded and individually adapted to each gLiFE participant’s functional level, also taking into account personal routines and environment as described by the participant, and using simulated demonstration instead of demonstration in the actual situation as provided in LiFE. Unlike LiFE, utilizing LiFE in a group may also enrich the program’s prosperity through psychosocial resources such as social interaction and mutual role-modelling of the participants [78, 79].

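### Group delivery in the gLiFE arm is ignored by the primary test: if outcomes correlate within groups, the one-sided error exceeds 5% (about 5.3% to 10% for an assumed ICC of 0.01 to 0.10)

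*Protocol article*

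**What the plan says.** **Delivery.** Randomisation is of individuals, in blocks of variable size (Protocol article, Allocation and blinding). In the same section, "gLiFE groups will be started once at least 8 and up to 12 persons are randomly allocated to this arm", provided that their schedules match. For these groups, "Each session is going to be led by one main and one co-trainer" (Group LiFE). The comparator differs: "In LiFE, the program will be taught in seven individual home visits within 11 weeks" (Individual LiFE), by one trainer per visit (Table 2).

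**Analysis.** The Statistical analyses section fixes the primary test: "A one-sided Pearson’s chi-square test will be used to test noninferiority with α = 0.05 in the fall incidence between LiFE and gLiFE", with a margin of −15.9%. No term for gLiFE group is attached to it. The section on data analysis and process evaluation does mention modelling variation between participants and groups, but not for the noninferiority test.

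**Sample size.** The Sample size section obtains 81 per arm from the same chi-square test and 108 after 25% dropout. It continues: "To account for an additional variance due to the multi-centre design we increased the sample size by 10" per cent, and adds a further safety margin whose size and purpose are not given, reaching 150 per arm. No ICC or design effect for groups appears.

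**The concern.** This is a partially nested design: one arm consists of small treatment groups, the other of single participants. Members of a gLiFE group have the same two trainers, the same sessions, the same calendar period and the same peers. If some groups do better than others for these reasons, outcomes within a group are positively correlated and the gLiFE estimate varies more than an independent-data formula allows.

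The authors see a possible group mechanism themselves: the Discussion says that the format may enrich the programme "through psychosocial resources such as social interaction and mutual role-modelling of the participants". Group cohesion is measured in gLiFE only (Table 4).

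An understated variance makes the confidence bound too tight. In a noninferiority trial that error favours the new format. The Discussion makes a recommendation of gLiFE depend on this test, so its error rate matters.

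**Working it through.** **Inputs from the protocol.** Reference value 79.4% ("we expect a decrease in fall incidence (expressed as falls per amount of PA) of 79.4% for LiFE"), used here as a proportion because the planned test needs one; margin 0.20 × 79.4 = 15.88 points; one-sided α = 0.05; groups of m = 8 to 12; 150 per arm; 25% dropout.

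**Assumptions.** Power is not stated; I take 80%. The ICC is not stated; I take 0.01 to 0.10.

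**1. Reproduce the plan's figure.**

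n = 2 × p(1−p) × (1.645 + 0.842)² / margin² = 2 × 0.1636 × 6.183 / 0.02522 = 80.2, rounded up to 81. Then 81 / 0.75 = 108.

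Both figures match. With the same formula, 90% power gives 111–112 and a one-sided α of 0.025 gives 102, so 80% and 0.05 are the settings that fit. The match uses a design effect of 1: the base calculation holds no allowance for groups.

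**2. Number of groups.** 150 / 12 = 12.5 and 150 / 8 = 18.75, so about 13 to 19.

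**3. Type I error of the independent-data test.** At the noninferiority boundary, pL = 0.794 and pG = 0.794 − 0.1588 = 0.6352. The variance terms are vL = 0.1636 and vG = 0.2317. Only gLiFE is inflated:

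DE = 1 + (m − 1) × ICC

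V = (vL + DE × vG) / (vL + vG)

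true α = 1 − Φ(1.645 / √V)

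Example with m = 10 and ICC 0.05: DE = 1.45; V = (0.1636 + 0.3360) / 0.3953 = 1.264; √V = 1.124; 1.645 / 1.124 = 1.463; α = 7.2%.

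| ICC | DE, m = 8 / 10 / 12 | True α, m = 8 / 10 / 12 | Simulated α, m = 10 |
|---|---|---|---|
| 0.01 | 1.07 / 1.09 / 1.11 | 5.3 / 5.4 / 5.5% | 5.5% |
| 0.02 | 1.14 / 1.18 / 1.22 | 5.7 / 5.9 / 6.1% | 6.0% |
| 0.05 | 1.35 / 1.45 / 1.55 | 6.7 / 7.2 / 7.6% | 7.3% |
| 0.10 | 1.70 / 1.90 / 2.10 | 8.3 / 9.2 / 10.0% | 9.4% |

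The simulation drew beta-binomial groups in gLiFE only, 150 per arm, 200,000 runs per setting. With no clustering it gave 5.1%.

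**4. Does a larger trial help?** The number per arm cancels from V, so the formula gives the same α at 81, 112 or 150 per arm. More groups of the same size do not correct it.

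**5. Does dropout help?** If a quarter of each group of 10 were lost, m = 7.5 and α would be about 5.3, 5.6, 6.6 and 8.1% at the four ICCs. The planned imputation of missing data complicates this, so it is indicative only.

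**6. Power.** 150 × 0.75 gives about 112 analysed per arm. Required n per arm = 40.10 × (1 + DE), where 40.10 = 0.1636 × 6.183 / 0.02522. Setting this to 112 gives DE = 1.793, hence ICC = 0.793 / (m − 1): 0.113, 0.088 and 0.072 for m = 8, 10 and 12. Below those values, power of a correctly adjusted large-sample test stays at or above 80%. For m = 10 it is 89%, 84% and 79% at ICC 0.01, 0.05 and 0.10.

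**The case against.** **The excess is conditional.** No ICC is given, and at 0.01 the excess is under one percentage point. A reader might infer that the error rate is known to exceed 5%. The documents do not support that: it follows only if the ICC is above zero. This objection stands, and the result is therefore given as a range.

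**The evidence for correlation is indirect.** The Discussion says only that the group may help. A benefit shared equally by all groups shifts the arm mean without creating variation between groups. Table 2 also says that dose depends on each person's own activity plan, which argues for a low ICC. This stands as a caution on size. It does not justify fixing the ICC at zero for people who share trainers, sessions and peers.

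**The sample size has slack.** A reader might infer that the trial is underpowered, or that 10% for centres is the only allowance. Neither holds. There is also an unspecified safety margin: 108 × 1.10 = 118.8, and 150 / 118.8 = 1.26 remains after the centre allowance. As step 6 shows, this largely absorbs the power loss. It does nothing for the error rate.

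**Trainers are shared in LiFE too.** Trainer effects can arise in both arms, and treating LiFE participants as singletons leaves them out there. This is fair, but it does not remove clustering by session group and peers, which exists in gLiFE only.

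**An analysis plan may deal with it.** Such a plan is not shown, and model details properly belong there. However, the protocol names a specific primary test that assumes independence. The objection is to that stated rule, not to a missing detail.

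**Conclusion.** The point holds in conditional form. The design groups participants in one arm only, and both the stated test and the base figure of 81 treat everyone as independent. For any positive ICC the test is anticonservative in the direction of a noninferiority claim. The excess over 5% runs from about 0.3 points (ICC 0.01, groups of 8) to about 5 points (ICC 0.10, groups of 12), somewhat less if dropout shrinks the groups. The consequence is for the error rate; power is little affected.

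The structure is certain from the text; the size is not. It rests on the assumed ICC range, equal full groups, the 79.4% taken as a binomial proportion, and 80% target power for the power statement. Whether a proportion is the right form for a fall rate is a separate question; group membership matters whichever outcome model is used.

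**What to change.** Whatever primary model is used, make the noninferiority test account for gLiFE group membership. Two suitable forms are:

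- a partially nested model with a group effect in the gLiFE arm only; or
- cluster-robust variance with each gLiFE group as a cluster and each LiFE participant as a singleton.

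Either needs a small-sample correction, because there will be only about 15 groups.

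Make sure that the group each gLiFE participant attended is recorded in the database; the protocol does not say that it is. State the assumed ICC and the resulting design effect alongside the sample size, so that the reader can see how much of the increase from 108 to 150 covers grouping.

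The cost is a slightly wider interval, one extra data item if it is not already held, and a revised statement of the primary test in place of the plain chi-square. On the figures above no additional participants are needed at ICCs up to roughly 0.07–0.11, although the small-sample correction will take a little of that margin.
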